### Study Design

Given the findings from previous case studies, a sequential mixed methods study design is suitable for use in this pre-post pilot study to explore congruences between psychometric, interview, and fMRI data regarding changes in hedonic capacity among individuals with anhedonia following the music therapy intervention. Neither a strictly explanatory nor exploratory model (according to Creswell and Plano [44] definitions) is used, but the design will prioritize quantitative data from psychometric scales and seek to understand any significant differences from before to after intervention using interview data collected after intervention. This will cautiously extend case study findings of the same music therapy intervention [21,22] to determine whether psychometric outcomes are significant at the group level, as well as to explore patterns in the interview data to better understand any changes on the 2 different outcome measures—the DARS [45] and the Snaith-Hamilton Pleasure Scale (SHAPS) [46]. It would be premature to include a control condition at this stage, and similarly, the sampling of participants will be restricted to high-functioning people with anhedonia to better understand the phenomenon before extending the research to more clinical populations, such as those with schizophrenia or MDD. In addition, the study will assess the feasibility of the intervention and study procedure to inform a subsequent larger-scale study [47]. Feasibility measures will evaluate the acceptability, adherence, and practicality of delivering the intervention in adults with high cognitive function, while preliminary estimates of intervention effects and variability will be used to inform sample size calculations and the design of a future fully powered study.

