### Eligibility Criteria

To identify participants with anhedonia, communications included a link to an online screening survey that prospective participants could independently access, comprising the DARS and questions assessing the inclusion criteria. The research team reviewed all survey responses, and eligible prospective participants were identified as scoring <44 on the DARS [45], based on the group differences identified between patients with major depressive episodes and healthy controls. This score has also been used in a study of university students where none of the healthy controls scored <44 points on the total scale [52]. All participants were required to complete a magnetic resonance imaging (MRI) safety implant checklist and be screened by qualified radiographers to deem them compatible with an MRI scan.

The inclusion criteria are being a professional, research, or academic member of the university community, having the cognitive capacity to select and discuss pleasure-inducing music, being aged >18 years, scoring <44 on DARS, agreeing to participate and having the capacity to provide informed consent, having a self-identified interest in music, and having English literacy skills suitable for participation in interviews. Exclusion criteria for all groups are failure to meet scanning requirements, including having metallic objects in the body (eg, a cardiac pacemaker or cochlear implant), a history of claustrophobia, permanent metal dental appliances, or a body weight ≥120 kg, or having a diagnosis of schizophrenia or MDD.

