Pre-post DARS scores are recorded during the screening survey and prior to the exit interview. This timing allows the scale to be used to determine participant eligibility for the study. Pre-post SHAPS scores are recorded on fMRI scanning days, as part of the prescan briefing process. This timing provides an indicator of hedonic capacity at the time of scanning. Pre-post score comparisons from these validated tools will also be used to assess changes in anhedonia severity in individual participants after the intervention.

Scanning sessions for fMRI data collection will be conducted on a 7T MAGNETOM Plus MRI system (Siemens Healthineers) located at the Melbourne Brain Centre Imaging Unit (MBCIU) at the University of Melbourne. Imaging will consist of (1) a structural scan, (2) resting-state fMRI, and (3) BOLD fMRI, using 4 tasks: reward reversal, music, naturalistic positive music, and naturalistic neutral music listening. These tasks have been specifically developed to target reward- and music-processing–related neurocircuitry, which are hypothesized to be relevant to our intervention.

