### Participant Timeline

The schedule for data collection is outlined in Figure 1. The DARS is independently completed online by participants who volunteer to participate. Questions on the online platform also confirm that they are professional, research, or academic members of the university community, aged >18 years, do not have a diagnosis of schizophrenia or MDD, and are interested in music. If these questions are confirmed and their score is <44 on the DARS, they are contacted by the research team to complete an intake interview, where this information is confirmed along with their English literacy skills, reflective cognitive capacity, and understanding of the requirements of the study. Times are then scheduled at the study center for further preintervention testing, including completion of the SHAPS and fMRI data acquisition. Brief interviews are conducted following the data acquisition to identify any feasibility issues with the music task. Following scans, participants commence 4 months of weekly meetings with the interventionist and undertake the daily music activities. Following completion of the intervention, participants return to the study center to complete the posttest measures of the DARS, SHAPS, and fMRI data acquisition and then participate in an exit interview.

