### Sample Size

A sample size of 13 was selected to provide adequate depth of qualitative data (interviews) while maintaining feasibility for resource-intensive fMRI data collection. This sample size is sufficient for exploratory mixed methods analysis and effect size estimation, although it is underpowered for statistical inference [53].

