### Data Analysis

Repeated-measures *t* tests will be conducted on pre-post DARS and SHAPS scores to examine directional change. Hedges *g* will be calculated to estimate effect sizes, which will inform power calculations for a future fully powered study. *P* values will be reported descriptively but not interpreted as indicators of statistical significance, given the small sample size (N=13).

fMRI data will be analyzed using individual general linear models to identify longitudinal changes associated with the intervention. For each task, blocked-design general linear model analyses will be specified at an individual participant level in Statistical Parametric Mapping version 12 (SPM12) to model specific conditions of interest. For the reward-reversal task, this will involve contrasting unexpected punishment trials with expected reward trials. For the music task, the primary contrast will compare pleasurable music with neutral music. Repeated-measures, flexible factorial designs (within-subject factors: primary contrast×time) will be used at the group level to examine longitudinal changes. These will then inform exploratory investigations of associations between these effects and symptom improvement.

Inductive thematic analysis will be used to identify patterns in descriptions of change and group similar ideas from across the interview data [58]. Labels will be selected that verifiably represent the participant quotes contained within each theme, and these will be checked by the research team as a form of peer debriefing to identify blind spots and adjusted when found to be dissimilar.

Sequential analysis will be conducted by comparing the themes from interviews to overall changes in participant scores on psychometric measures of anhedonia from preintervention to postintervention assessments to identify any correspondences. Themes will also be compared to any changes in activity across reward processing regions during reward fMRI tasks and targeted music listening evident from preintervention to postintervention assessments that correspond with patterns of congruence in the psychometric data.

Feasibility will be documented based on verbal feedback following fMRI data acquisition and in the final interview. Anything beyond individual preferences will be used to inform necessary changes to the protocol.

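### The screening DARS, cut at 44, is also the pre score, so its SD (alone or pooled with the post SD) should not standardise the effect size used to plan the next trial

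*Protocol article*

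**What the plan says.** Eligibility Criteria: "eligible prospective participants were identified as scoring <44 on the DARS". Participant Timeline repeats the rule: the research team contacts volunteers if "their score is <44 on the DARS" and the other screening questions are confirmed.

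Outcomes makes that reading the baseline: "Pre-post DARS scores are recorded during the screening survey and prior to the exit interview". The reason given is that "This timing allows the scale to be used to determine participant eligibility for the study". No second DARS before the intervention is described. The SHAPS, by contrast, is taken on the scanning days and does not decide entry.

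Data Analysis says that repeated-measures t "tests will be conducted on pre-post DARS and SHAPS scores to examine directional change", and that Hedges g "will be calculated to estimate effect sizes, which will inform power calculations for a future fully powered study". Study Design adds variability to what is carried forward: "preliminary estimates of intervention effects and variability will be used to inform sample size calculations and the design of a future fully powered study". Neither section says which SD divides g or which SD is meant by variability. Limitations names the small sample and the missing control group, but not the effect of the cut-off on the spread of scores.

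**The concern.** Removing everyone at 44 or above narrows the pre score. The post score has no cut of its own and is narrowed only through its correlation with the pre score, so its SD is larger. A later controlled trial that compares arms at follow-up works with that larger SD.

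Two common choices for a pre-post g are the baseline SD and the pooled pre/post SD. Both contain the narrowed reading. This is separate from regression to the mean, which affects the numerator. A control group, or a corrected mean change, would leave the denominator as it is. At stake is the size of the next trial, which is the stated use of these estimates.

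**Working it through.** **The plan's own figure.** There is none to reproduce. The sample of 13 rests on qualitative depth and imaging feasibility, and the article gives no DARS SD, correlation, effect size, alpha or power.

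**From the article.** Cut-off below 44 on the screening DARS; the same reading is the pre score; N = 13; g and variability feed the next sample size.

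**Assumed.** Pre and post scores are bivariate normal with unrestricted SD 1 and correlation r = 0.7 to 0.9. The intervention shifts scores uniformly. The cut lies at c = 0 to −1.5 SD from the screened population's mean.

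**Formulas.** With λ = φ(c)/Φ(c):
- pre variance v = 1 − cλ − λ²
- post variance q = r²v + 1 − r²
- pooled variance (v + q)/2
- change variance (1 − r)²v + 1 − r²; without selection, 2(1 − r)

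**One case in full (c = −1, r = 0.8).** λ = 0.2420/0.1587 = 1.525. v = 1 + 1.525 − 2.326 = 0.199, pre SD 0.446. q = 0.64 × 0.199 + 0.36 = 0.487, post SD 0.698. Pooled SD = √0.343 = 0.586. So g is inflated by 0.698/0.446 = 1.57 with the pre SD and by 0.698/0.586 = 1.19 with the pooled SD. Change SD = √(0.04 × 0.199 + 0.36) = 0.607, against √0.4 = 0.632 without selection, a ratio of 0.96.

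**Corners of the grid.**

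| c | r | pre SD | post SD | post/pre | post/pooled |
|---|---|---|---|---|---|
| 0 | 0.7 | 0.603 | 0.829 | 1.38 | 1.14 |
| 0 | 0.9 | 0.603 | 0.696 | 1.15 | 1.07 |
| −1.5 | 0.7 | 0.387 | 0.764 | 1.97 | 1.26 |
| −1.5 | 0.9 | 0.387 | 0.558 | 1.44 | 1.16 |

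Relative to the post SD, g is therefore 15% to 97% too large with the pre SD and 7% to 26% too large with the pooled SD. Sample size goes with the square of the SD. For an unadjusted comparison of post scores it would be understated 1.33- to 3.9-fold with the pre SD and 1.14- to 1.6-fold with the pooled SD.

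**Change SD.** Over this grid it is 0.93 to 0.98 of its unselected value. Widening the range to r = 0.5 and 5% of the source population below the cut-off lowers that to 0.886, about 11% too small. Under the same cut-off in the next trial, this bias is nil.

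**Illustration.** Assume 10% of the source population below the cut-off, r = 0.7, and a true effect of 0.5 post SD, two-sided 5%, 80% power. Per arm, 2 × (1.96 + 0.84)²/0.5² gives 63. The SDs are pre 0.41, pooled 0.62, post 0.77. The same raw difference planned with the pre SD gives 18 per arm, with the pooled SD 41, with the post SD 63. A simulation of this case gave 0.412 for the pre and 0.770 for the post SD.

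**Sampling error at N = 13.** The 95% limits for any SD are √(12/23.34) = 0.72 and √(12/4.40) = 1.65 times the estimate.

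**The case against.** The strongest reply is that the article makes no wrong choice. It names no standardiser, and a condensed article may leave that to the analysis plan. The only SD implied by a stated method is the SD of change, through the paired t test, and that SD is hardly affected. This stands. A reader might infer that the plan has already committed to a biased denominator, or that the next trial will be too small. The documents do not support either inference. They show only that one truncated reading serves as both entry gate and baseline, and that its variability is promised for planning without restriction.

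A second reply is that a baseline-adjusted trial depends on the residual variance 1 − r², which truncation leaves alone. Over the grid that variance is 0.45 to 1.39 times the pooled variance, and below 1 in 7 of 12 cells, so an undiscounted pooled SD could make such a trial too large. The arithmetic is right. But planning a baseline-adjusted analysis would normally discount by the observed correlation, which the cut also lowers, to r√(v/q). The pooled variance so discounted is 0.63 to 0.88 of the true residual variance, still too small. The post variance so discounted is q − r²v = 1 − r², exactly right.

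Third, every magnitude rests on an assumed cut position and correlation, and sampling error at N = 13 (0.51- to 2.7-fold in sample size) exceeds the pooled-SD bias. That also stands. The direction, pre SD < pooled SD < post SD, holds in every case examined. Sampling error can fall either way, whereas the cut always pulls one way.

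Finally, the article calls these estimates preliminary and the study underpowered for inference, and the SHAPS gives a second effect size that is not cut directly. This limits the consequence but does not correct a DARS g built on the screening SD.

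**Conclusion.** The point holds in conditional form. If the DARS g or SD carried forward uses the screening SD, or a pooled SD containing it, it is too favourable even with a correct mean change: about 7% to 26% for the pooled SD and 15% to 97% for the pre SD, under the stated assumptions. The upper figure, and the 3.9-fold sample size that goes with it, is one corner of the grid and not an expected value.

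A reader might infer that every SD from this pilot is unusable. That goes too far. For a next trial with the same DARS cut-off, the post SD and the change SD are the relevant quantities and the cut does not bias them. If selection differs, the change SD is at most about 11% too small in the range examined. The post SD, however, is then 0.56 to 0.83 of the unrestricted SD, which matters because the article also foresees moving to other clinical populations. This is an inexpensive improvement to the plan; the actual harm cannot be determined while the divisor is unnamed.

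**What to change.** In Data Analysis:
- Report the raw DARS mean change, pre SD, post SD, change SD and pre-post correlation, each with a confidence interval.
- State that any DARS g or SD used to plan the next trial takes the post SD, or the change SD where the next trial will analyse change scores, and not the screening or pooled SD.
- State that these figures apply to a next trial with the same DARS cut-off.

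Planning from an upper confidence limit of the SD (the one-sided 80% limit is √(12/7.81) = 1.24 times the estimate at N = 13) is optional. It guards against small-sample error, not against the cut.

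No new data are needed. Data collection has ended, so a second pre-intervention DARS is no longer possible here, but analysis was still to come by the end of 2026. The cost is a few sentences and some extra summary figures. The DARS effect will look smaller and the next trial will be planned larger.

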## Methods

### Study Setting

Participants were recruited from within the authors’ research-led university, with advertisements being shared through formal and informal communication channels. The intention was to recruit participants who were able to complete the psychometric measures, commit to a daily musical activity routine, meet regularly with the music therapist to discuss practice experiences and plan for subsequent practices, and reflect on and provide subjective feedback on the intervention after it was concluded. Given these high demands, the study targeted staff and PhD students, and expectations were negotiated transparently before commencement.

### Ethical Considerations

This study was approved by the University of Melbourne Humanities, Arts, and Social Sciences (HASS) 2 Human Ethics Committee (27796), and plain language information was provided explaining the full extent of required participation and the limits of the evidence. Participation was not incentivized with payments, but the potential to participate in a novel intervention potentially motivated participation since there is minimal treatment available. Extended written consent was received from all participants, meaning that data or information used in this research project may also be used in future projects that are closely related to this project, are in the same general area, or could make valuable use of this data. Participant privacy and confidentiality were protected by processes of deidentification of data using a simple coding system, with all identifying information being stored in a password-protected file accessible only to the researchers.

### Eligibility Criteria

To identify participants with anhedonia, communications included a link to an online screening survey that prospective participants could independently access, comprising the DARS and questions assessing the inclusion criteria. The research team reviewed all survey responses, and eligible prospective participants were identified as scoring <44 on the DARS [45], based on the group differences identified between patients with major depressive episodes and healthy controls. This score has also been used in a study of university students where none of the healthy controls scored <44 points on the total scale [52]. All participants were required to complete a magnetic resonance imaging (MRI) safety implant checklist and be screened by qualified radiographers to deem them compatible with an MRI scan.

The inclusion criteria are being a professional, research, or academic member of the university community, having the cognitive capacity to select and discuss pleasure-inducing music, being aged >18 years, scoring <44 on DARS, agreeing to participate and having the capacity to provide informed consent, having a self-identified interest in music, and having English literacy skills suitable for participation in interviews. Exclusion criteria for all groups are failure to meet scanning requirements, including having metallic objects in the body (eg, a cardiac pacemaker or cochlear implant), a history of claustrophobia, permanent metal dental appliances, or a body weight ≥120 kg, or having a diagnosis of schizophrenia or MDD.

### Intervention

The music therapy intervention involves a 4-month process of therapeutic guiding through engagement with daily pleasure-focused music activities, developed through preliminary case studies in which a qualified music therapist works collaboratively with a participant to support and scaffold their process [21,22].

The therapist meets each participant weekly, which gradually tapers off after 8 weeks toward the closure of each participant’s process depending on their needs. These weekly meetings are typically 30 to 60 minutes long and designed to offer a supportive space where participants can share and reflect on experiences in their lives related to anhedonia and explore the ways they relate to pleasure in music. The meetings are also used to discuss the pragmatic aspects of daily pleasure-focused music engagement and collaboratively develop plans, with the intention of removing anhedonia-related barriers to participation. The process is tailored and flexible to the participant’s presenting needs and interests and may vary considerably depending on a range of factors, including but not limited to the level of support needed to identify pleasure-inducing music and music activities, needs related to safe engagement with emotionally potent music, and the degree to which the setting and context surrounding the activities create barriers or facilitate engagement.

Daily music activities of approximately 5 minutes are planned with each participant. This often begins with music listening due to ease of access and can expand to more active engagement, such as playing instruments, singing, or moving to music. Activities are flexibly tailored each week according to the participants’ emergent process and are designed to reduce identified barriers to promote their access to pleasurable feelings during these activities. Participants are also invited to complete a brief daily survey before and after their music activity. This includes pre-post ratings (from 1 to 10) of their anticipation and experience of pleasure during the activity, and a space for brief descriptive reflection. This aspect of the intervention is not compulsory but aims to invite participants’ cognitive engagement with their daily pleasure experience.

In addition to weekly meetings, participants also receive daily prompts via SMS or WhatsApp text message for the first 8 weeks from the music therapist to remind them of their plan for that day. These texts may draw on the words the person uses to describe their feelings of joy or pleasure in music and may include links to music where this reduces access barriers. An example of a SMS or WhatsApp text message reads as follows:

Hi [participant’s name], I hope your day is starting out well. Just a reminder for your pleasure-focussed music activity: listening to a song during your mid-morning break and tuning in to any feelings of joy, playfulness or creativity that might arise. [Song link provided]. Happy listening!

Closure of the intervention process is collaboratively planned, typically in the second half of the 4-month process, where participants are supported to increase their independence and autonomy in daily pleasure-focused music activities. This occurs through a gradual reduction of therapeutic scaffolding. Resources may be developed with the participant in the closure phase to support continued engagement with pleasure-focused music activities, for example, developing playlists of pleasure-inducing tracks used successfully during the process.

